### ***End of Treatment***

Subjects should be encouraged to complete as many of the 4 cycles of therapy as possible. The median time to response for both single agents is more than 100 days, thus maximal benefit will only be achieved from the full course. If a subject is removed from treatment for any reason, the subject must undergo end of treatment procedures. The end of treatment procedures include clinical laboratory investigations (chemistry and hematology), urine pregnancy testing, and adverse event assessment.

If a subject is removed from treatment prior to completing 4 cycles due to excessive toxicity the subject remains on TA assessments as per section 4.1.2.

If a subject elects to come off treatment by withdrawing consent before completing 4 cycles, the reason for withdrawal must be entered on the appropriate case report form (CRF) page.

### ***4.1.2 Tumor Assessments (TA)***

Tumor assessment with radiographic imaging (e.g. MRI-CT of brain, CT of chest, abdomen, pelvis, other soft tissues) and digital photographs of skin lesions will be performed for all subjects at Screening, week 12, then every 6 weeks at weeks 18, 24, and every 12 weeks from week 24 onwards, for all non-progressing subjects. At each evaluation investigators will assess the overall response (complete response (CR), partial response (PR), stable disease (SD) or Progressive Disease (PD) (as categorized by irRC).

#### ***4.1.2.1 Confirmed ir-Disease Progression***

Unless they are rapidly deteriorating, those patients who experience ir-disease progression, as determined by the investigator, should have confirmation of irPD at the next scheduled TA (see Tab.6.1). Increases in lesion size detected radiologically or upon gross examination could be misinterpreted as progressive tumor growth since ipilimumab can produce an influx or expansion of tumor infiltrating lymphocytes. Therefore no subsequent anti-cancer treatment should be given prior to confirmed irPD. See Section 6.4.

#### ***4.1.2.2 Tumor Assessment Schedule Rationale***

Ipilimumab is expected to trigger immune-mediated responses, which require activation of the immune system prior to the observation of clinical responses. Such immune activation may take weeks to months. Some patients with advanced melanoma may have objective volume increase of tumor lesions within 12 weeks after inclusion in the study. Such patients may have not had sufficient time to develop the required immune activation or, in some patients, tumor volume increases may represent infiltration of lymphocytes into the original tumor. In conventional studies, such tumor volume increases during the first 12 weeks of the study would constitute PD and lead to discontinuation of imaging to detect response, thus disregarding the potential for subsequent immune-mediated clinical response. Therefore, in this study, patients with tumor volume increase detected at Week 12 but without rapid clinical deterioration will continue to be clinically observed with a stringent imaging schedule to allow detection of a subsequent tumor response. This will improve the overall assessment of the clinical activity of ipilimumab and more likely capture its true potential to induce clinical responses. Tumor assessments will be made using the immune-related (ir) tumor response criteria. See Sections 6.4.3.5.

### ***4.1.3 Safety Assessment***

#### ***Safety Monitoring Committee***

A Safety Monitoring Committee (SMC) will be established for the trial.

The SMC will monitor subjects' safety and will review all reported adverse events (AEs) and serious adverse events (SAEs) on an ongoing basis throughout the trial. Information on all SAEs and potential dose-limiting toxicities (DLTs) will be sent to the SMC by the end of the business day on which documented information on SAEs or DLTs was received. Enrollment of subjects into a respective cohort will be paused when the first 3 subjects have entered the first treatment cycle. A full safety data set (all AEs including SAEs, laboratory safety data, vital signs and available pharmacokinetic and pharmacodynamic data) from at least the first 3 weeks (i.e., up to Day 22, until the second cycle of SGI-110 dosing) will be submitted to the SMC.

The SMC will decide, by consensus, on DLTs relevant for the respective combination treatment, and will decide, by consensus, on dose and schedule escalation, dose and schedule de-escalation, dose and schedule expansion, suspension of enrolment, and declaration of the maximum tolerated dose (MTD) for the respective combination treatment.

DLTs are defined in Section 5.3. The process by which the MTD will be defined is described in Section 5.2.2

#### 4.1.4 Study Schema

| COHORT   | SGI-110
Day 1-5 q 3w | Ipilimumab
Day 1 q 3w |
|------------------------|----------------------------------------|-----------------------------------------|
| Level -1 | 15mg/kg s.c.             | 3 mg/kg i.v.              |
| Level 0  | 30mg/kg s.c.             | 3 mg/kg i.v.              |
| Level +1 | 45mg/kg s.c.             | 3 mg/kg i.v.              |
| Level +2 | 60 mg/kg s.c.            | 3 mg/kg i.v.              |

*q3w= every 3 weeks;*

Figure 2

#### 4.1.5 Rationale for starting dose and for dose escalation schema

At an SGI-110 daily dose range of 60-90 mg/m^2, the observed 5-AZA-CdR AUCs reached or exceeded the therapeutic range seen with IV 5-AZA-CdR (20 mg/m^2) with a lower Cmax, but a longer effective half-life and exposure window. Dose-related increases in LINE-1 demethylation after SGI-110 dosing was observed in the majority of subjects treated with the Daily x5 regimen between 18 and 60 mg/m^2 day

doses and significant reductions were seen at 36 mg/m^2. Maximum average demethylation (~25%) plateaued after 60 mg/m^2, with daily doses (90-125 mg/m^2) showing no further increase. Therefore the BED for the Daily x5 regimen was established at 60 mg/m^2.

The rationale for selection of the starting dose of SGI-110 for this study is based on previous experience with decitabine in ovarian cancer  and emerging data from the Phase 1/2 study of SGI-110 (Study SGI-110-01). The single agent experience in myeloid malignancies was in 28 day cycles. In the Phase 1/2 study of SGI-110, the daily regimen up to 90 mg/m^2 daily x5 was well tolerated with no DLTs. Based on this evidence, the starting dose of the proposed study here is 30 mg/m^2 daily x5, also, due to the 1 week shorter recovery period between dosing investigated in this trial; though no overlapping myelosuppression with ipilimumab is expected. Dose de-escalation to 15 mg/m^2 daily x5 or escalation to 45 -60 mg/m^2 day x5 will be based on the tolerability of the each cohort of 3-6 subjects.

#### ***4.1.6 Duration of Study***

We assume a planned uniform accrual period of 24 months and a follow-up period of 24 months. Patients will be treated until the prescribed 4 cycles of therapy or until ir Progressive Disease (PD), excessive toxicity, or patient refusal. Upon completion of treatment, all subjects will be followed with efficacy assessments until PD and for survival until 2 years post Last Patient First Visit. The total study duration will be approximately 48 months.

## **4.2 Study Population**

For entry into the study, the following criteria MUST be met within 4 weeks prior to first dose. Any exemptions from the protocol-specific section criteria must be approved by the Principal Investigators and/or Institutional Review Board (IRB) before enrollment.

### ***4.2.1 Inclusion Criteria***

#### ***Signed Written Informed Consent***

Willing and able to give written informed consent.

#### ***Target Population***

- 1) Subjects must fulfill all of the following inclusion criteria:
- 2) Unresectable Stage III or Stage IV melanoma with measurable lesions by CT or MRI per mWHO/irRC criteria, that can be amenable to biopsy

- 3) Previously treated or untreated; prior therapy may include chemotherapy or targeted therapy for metastatic disease (i.e., BRAF and/or MEK inhibitor). Prior adjuvant interferon is permitted.
- 4) Subjects with ECOG performance status of 0 to 1
- 5) 4 weeks or greater since last treatment
- 6) Must have recovered from any acute toxicity associated with prior therapy
- 7) Life expectancy greater than 16 weeks
- 8) Subjects with adequate organ function defined as:
  - 9) WBC  $\geq 3500/\mu\text{L}$
  - 10) ANC  $\geq 2000/\mu\text{L}$
  - 11) Platelets  $\geq 100 \times 10^3/\mu\text{L}$
  - 12) Hemoglobin  $\geq 9 \text{ g/dL}$
  - 13) Creatinine  $\leq 2.5 \times \text{ULN}$
  - 14) AST  $\leq 2.5 \times \text{ULN}$  for patients without liver metastasis  
 $\leq 5 \times \text{ULN}$  for patients with liver metastasis
  - 15) Bilirubin  $\leq 1.5 \times \text{ULN}$  for patients without liver metastasis  
 $\leq 3 \times \text{ULN}$  for patients with liver metastasis  
 $<3.0 \text{ mg/mL}$  for patients with Gilbert's Syndrome
- 16) Negative screening tests for HIV, HepB, and HepC. If positive results are not indicative of true active or chronic infection, the patient can enter the study after discussion and agreement between the Investigator and the Medical Monitor.
- 17) Women of child-bearing potential must not be pregnant or breastfeeding, must have a negative pregnancy test at Screening and all men must be practicing two medically acceptable methods of birth control. Men should not father a child while receiving treatment with SGI-110 + ipilimumab, and for 2 months following completion of treatment. Men with female partners of childbearing potential should use effective contraception during this time.

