### ***5.2.1 Dosage and Administration***

#### ***SGI-110 schedule***

SGI-110 will be administered:

Start at 30 mg/m^2 day s.c. on W0, 3, 6, 9 Day 1 - 5 q21 days. Dose Level -1: 15 mg/m^2 day; dose level +1: 45 mg/m^2 day, Dose Level +2: 60 mg/m^2 day for a total of 4 cycles.

SGI-110 is administered by SC injection preferably in the abdominal area; however the thigh and arms may be used. A Luer-Lok disposable syringe should be used when dispensing and administering SGI-110. Due to the slightly viscous nature of the preparation, use of thin-walled subcutaneous needle is highly recommended for ease of subcutaneous administration and subject comfort. SGI-110 should be injected slowly (up to one minute) as some injection site discomfort or pain may be experienced.

If injection site pain is reported upon injection, apply ice packs to the injection site both before and after injection. If the injection site events are reported at subsequent injections despite slow injection and the use of ice packs, pre-treatment with topical or systemic analgesics can be considered. The total amount (in mg) of SGI-110 to be administered will be determined based on the body surface area (BSA). In calculating the BSA, actual heights and weights taken at enrolment should be used. There will be no adjustments to “ideal” body weight or dose modifications related to changes in body weight < +/- 10%. The institutional standard for calculating BSA is acceptable.

The site(s) of SGI-110 SC injections will be captured on the dosing CRF.

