#### ***Ipilimumab schedule***

Ipilimumab will be administered:

3 mg/Kg i.v. over 90 minutes on W1, 4, 7 and 10 for a total of 4 cycles.

Ipilimumab is to be administered as a 90-minute IV infusion, using a volumetric pump with a 0.2/0.22 micron in-line filter at the protocol-specified dose. The drug can be diluted with 0.9% normal saline for delivery but the total drug concentration of the solution cannot be below 0.35 mg/ml. It is not to be administered as an IV push or bolus injection. At the end of the infusion, flush the line with a sufficient quantity of normal saline.

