## **5.3 Dose-limiting Toxicity**

DLT is defined as any of the following events occurring during the first treatment cycle and clearly related to study treatment: grade 4 neutropenia (absolute granulocyte count < 0.5 x 10^9/L, ≥ 5 days), febrile neutropenia grade ≥ 3 (absolute granulocyte count < 1.0 x 10^9/L and fever ≥ 38.5° C), platelet count < 25.000/L or thrombocytopenic bleeding, AST or ALT grade ≥ 3 for 7 days, any grade 3 or 4 non-hematologic toxicity (excluding alopecia, non pre-medicated nausea and vomiting), grade 3 or 4 clinically

significant nausea, vomiting, or diarrhoea in the presence of maximal supportive care, a required interruption of treatment > 2 weeks due to toxicity. If the toxicity fails to resolve to  $\leq$  grade 2 with 14 days off treatment, the patient will be removed from the study.

Inability to initiate Cycle 2 within 2 weeks of scheduled treatment due to slow recovery from study drug-induced toxicities and failure to meet re-treatment criteria.

The DLT observation period is defined as the first 3 weeks of treatment, i.e., from Day 1 to Day 21 of Cycle 1. Once the MTD is reached in each group, the safety data will be analysed.

Note: All AEs (including those occurring after the end of the DLT observation period) will be considered for decision-making by the SMC.

**Tolerability** will be defined as the ability to continue treatment for at least 2 cycles in a row without development of DLTs.

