### ***5.3.2 Discontinuation Criteria***

#### ***Ipilimumab Permanent Discontinuation***

Treatment should be permanently discontinued for the following:

- Any Grade 2 drug-related uveitis or eye pain or blurred vision that does not respond to topical therapy and does not improve to Grade 1 severity within the re-treatment period OR requires systemic treatment
- Any Grade 3 non-skin, drug-related adverse event lasting > 7 days, including uveitis, pneumonitis, bronchospasm, diarrhea, colitis, neurologic adverse event, hypersensitivity reactions, and infusion reactions. Drug-related laboratory abnormalities are exceptions, as discussed below.
  - Grade 3 drug-related uveitis, pneumonitis, bronchospasm, diarrhea, colitis, neurologic adverse event, hypersensitivity reaction, or infusion reaction of any duration requires discontinuation
  - Grade 3 drug-related laboratory abnormalities do not require treatment discontinuation except those noted below
    - a. Grade 3 drug-related thrombocytopenia > 7 days or associated with bleeding requires discontinuation
    - b. Any drug-related liver function test (LFT) abnormality that meets the following criteria require discontinuation:
      - AST or ALT > 8 x ULN
      - Total bilirubin > 5 x ULN
      - Concurrent AST or ALT > 3 x ULN and total bilirubin > 2 x ULN
- Any Grade 4 drug-related adverse event or laboratory abnormality, except for the following events which do not require discontinuation:
  - Isolated Grade 4 amylase or lipase abnormalities that are not associated with symptoms or clinical manifestations of pancreatitis and decrease to < Grade 4 within 1 week of onset.
  - Isolated Grade 4 electrolyte imbalances/abnormalities that are not associated with clinical sequelae and are corrected with supplementation/appropriate management within 72 hours of their onset
- Any dosing interruption lasting > 6 weeks with the following exceptions:
  - Dosing interruptions to allow for prolonged steroid tapers to manage drug-related adverse events are allowed. Prior to re-initiating treatment in a subject with a dosing interruption lasting > 6 weeks, the Investigator must be consulted. Tumor assessments should continue as per protocol even if dosing is interrupted

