### ***Liver Function Tests (LFT) Assessments Required Prior to Administration of ipilimumab***

Liver function tests (AST, ALT, T. bilirubin) will be evaluated for every subject prior to administration of ipilimumab. Blood samples must be collected and analyzed at local or central labs within 3 days prior to dosing. LFT results must be reviewed by the principal investigator (or designee) to meet dosing criteria specifications:  $\leq 3 \times \text{ULN}$  for AST, ALT and  $\leq 1.5 \times \text{ULN}$  for T. bilirubin unless liver metastases are present in which case  $\text{LFT} \leq 5 \times \text{ULN}$  for AST, ALT and T. bilirubin  $\leq 3.0 \times \text{ULN}$  prior to dosing.

Although infrequent, liver toxicity may be associated to the administration of SGI-110. It could possibly occur around Week 4 or 5. Special attention should thus be paid to LFT results prior to the ipilimumab dosing on Weeks 4 and 7.

If, during the course of treatment abnormal LFT values are detected, the subject must be managed using the hepatotoxicity algorithm section of the ipilimumab Investigators Brochure.

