| Timepoint                                                                                             | Day -28 to Day-1 | Wk 0 | Wk 1                                      | Wk 2 | Wk 3 | Wk 4 | Wk 6 | Wk 7 | Wk 9 | Wk 10 | Wk 12           | Wk 18 | Wk 24 | Wks 36+ |                         |                         |
| Visit                                                                                                 | 0                | 1    | 2                                         | 3    | 4    | 5    | 6    | 7    | 8    | 9     | 10              | 11    | 12    | 13      |                         |                         |
| Laboratory Tests                                                                                      |                         |             |                                                  |             |             |             |             |             |             |              |                        |              |              |                |                         |                         |
| Chemistry & Hematology (prior to dosing)                                                          | X                       | X           | X                                                | X           | X           | X           | X           | X           | X           | X            | X                      | X            | X            | X              | X                       | 6.3.7.16
.3.7.2      |
| Urine analysis                                                                                        | X                       |             |                                                  |             |             |             |             |             |             |              |                        |              |              |                |                         |                         |

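### Entry liver criteria set no ALT limit and, without liver metastases, allow a Gilbert's bilirubin above the level at which ipilimumab must be withheld

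*Combined protocol and SAP*

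**What the plan says.** **Entry (4.2.1, Target Population, items 14–15).** AST must be at or below 2.5 × ULN, or 5 × ULN with liver metastases. Bilirubin must be at or below 1.5 × ULN, or 3 × ULN with liver metastases. For Gilbert's syndrome the bilirubin limit is "<3.0 \text{ mg/mL}$ for patients with Gilbert's Syndrome". ALT does not appear in the organ-function list, and the exclusion criteria in 4.2.2 add no ALT limit.

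**Before ipilimumab (5.3.2, liver function tests).** "Liver function tests (AST, ALT, T. bilirubin) will be evaluated for every subject prior to administration of ipilimumab". The limits are AST and ALT at or below 3 × ULN, and 1.5 × ULN "for T. bilirubin unless liver metastases are present in which case" they become 5 × ULN for AST and ALT and 3.0 × ULN for bilirubin. Liver metastases are the only exception.

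**Order of dosing (5.2.1).** SGI-110 is given "s.c. on W0, 3, 6, 9 Day 1 - 5 q21 days". Ipilimumab is given "3 mg/Kg i.v. over 90 minutes on W1, 4, 7 and 10 for a total of 4 cycles". The first SGI-110 course therefore comes before the first ipilimumab check.

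**Other liver rules.** The DLT definition in 5.3 counts "AST or ALT grade ≥ 3 for 7 days". Permanent discontinuation in 5.3.2 is triggered by "AST or ALT > 8 x ULN". The ipilimumab delay rules in 5.3.1 and the chemistry section 6.3.7.1 also name both enzymes.

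**The concern.** Entry criteria for a combination trial should not admit a patient whose known baseline value already fails the dosing rule for one of the two drugs. Here two such values pass: a raised ALT with an acceptable AST, and a Gilbert's bilirubin that 4.2.1 accepts but 5.3.2 does not.

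At stake is a small number of patients who would start SGI-110 and then be refused ipilimumab at Week 1 for something visible at screening. The primary objective concerns the combination. Section 8.2 defines the full analysis set as subjects with at least one dose of SGI-110 and ipilimumab, so a patient who never receives ipilimumab drops out of it.

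**Working it through.** No sample-size or power figure bears on this point. The check sets the two sections side by side and converts one unit.

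**Step 1. Limits compared.**

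| Test | Entry (4.2.1) | Before ipilimumab (5.3.2) | Entry is |
|---|---|---|---|
| AST, no liver metastases | ≤ 2.5 × ULN | ≤ 3 × ULN | tighter |
| AST, liver metastases | ≤ 5 × ULN | ≤ 5 × ULN | the same |
| ALT, no liver metastases | none | ≤ 3 × ULN | looser |
| ALT, liver metastases | none | ≤ 5 × ULN | looser |
| Bilirubin, no liver metastases | ≤ 1.5 × ULN | ≤ 1.5 × ULN | the same |
| Bilirubin, liver metastases | ≤ 3 × ULN | ≤ 3.0 × ULN | the same |
| Bilirubin, Gilbert's, no liver metastases | < 3.0 (unit printed mg/mL) | ≤ 1.5 × ULN | looser (Step 3) |

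**Step 2. ALT.** The patients affected, if the value is unchanged by Week 1, are those with ALT above 3 × ULN and AST at or below 2.5 × ULN (no liver metastases), or ALT above 5 × ULN and AST at or below 5 × ULN (liver metastases). Every other liver rule listed above names ALT with AST; 4.2.1 alone names only AST. That suggests an omission rather than a choice.

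**Step 3. Gilbert's bilirubin.** The documents give no bilirubin ULN. I assume 1.0–1.2 mg/dL and show higher values.

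- As printed: 3.0 mg/mL × 100 = 300 mg/dL, or 250–300 × ULN at a ULN of 1.2–1.0 mg/dL. This excludes nobody.
- Read as mg/dL, the break-even ULN is 3.0 / 1.5 = 2.0 mg/dL. Below that, the entry limit is above 1.5 × ULN.

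| Assumed ULN (mg/dL) | 1.5 × ULN (mg/dL) | 3.0 mg/dL as a multiple of ULN |
|---|---|---|
| 1.0 | 1.5 | 3.0 |
| 1.2 | 1.8 | 2.5 |
| 1.5 | 2.25 | 2.0 |
| 2.0 | 3.0 | 1.5 |

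At a ULN of 1.0–1.2 mg/dL, the affected band is above 1.5–1.8 and below 3.0 mg/dL. Correcting the unit alone does not close it. With liver metastases, the break-even is 3.0 / 3.0 = 1.0 mg/dL, so there is no gap at a ULN of 1.0 mg/dL or more.

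The Gilbert's line cannot sensibly be an extra cap on top of 1.5 × ULN. At these ULNs and without liver metastases, 1.5–1.8 mg/dL would always bind first. It works only as an allowance, which 5.3.2 then takes away.

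**Step 4. Sequence.** Week 0: five daily SGI-110 injections. Week 1: liver check, then ipilimumab. A patient from Step 2 or 3 whose value has not fallen completes the first and fails the second.

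**The case against.** The best defence is that entry limits and per-dose limits serve different purposes and need not match. The later check works as intended: nobody receives ipilimumab at a liver value that 5.3.2 forbids. Chemistry is scheduled at Screening and Week 0 (6.1). Section 6.3.7.1 requires ALT, AST and bilirubin to be reviewed before either drug. Section 4.2.2 excludes patients with contraindications to ipilimumab, and 4.2.3 lets the investigator stop treatment. An attentive investigator would probably not start such a patient.

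This stands as a reason for low severity. It does not close the gap, because none of these provisions gives an ALT or bilirubin number that would keep the patient off SGI-110. What counts as a contraindication lies in product documents outside the protocol.

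A reader might infer several stronger things that the documents do not support:

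- *That a stable Gilbert's bilirubin fails all four ipilimumab checks.* Section 5.3.2 calls for permanent discontinuation after an interruption of more than 6 weeks, with an investigator-approved exception for reasons not related to drug. A hold from Week 1 reaches 6 weeks at Week 7 (1 + 6), before the Week 10 dose. Whether withholding a first dose counts as an interruption is not stated.
- *That the patient carries on with SGI-110 alone.* Only the Cycle 1 course is certain. No rule says what happens to later SGI-110 cycles after a failed liver check. The rules in 5.3.1 that delay all study drugs concern drug-related events, and the note in 4.2.3 on continuing one drug concerns excessive toxicity from the other.
- *That the unit is a proven misprint.* It is an inference from the size of the number; a fault in reading the PDF cannot be excluded. The mismatch remains under either unit.

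**Conclusion.** The point holds in two respects: no ALT limit at entry, and a Gilbert's bilirubin limit above 1.5 × ULN for patients without liver metastases. It should not be read as a general looseness of the entry liver criteria, since the remaining limits match or are tighter at entry.

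The established consequence is narrow. A patient can meet every numeric entry limit, receive the Cycle 1 SGI-110 course and be refused the first ipilimumab dose for a value known at screening. This assumes that the value has not fallen by Week 1 and, for Gilbert's, that the laboratory's ULN is below 2.0 mg/dL. A raised ALT may fall and allow ipilimumab later. If ipilimumab is never given, the patient is outside the full analysis set.

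A reader might infer that the MTD is affected. The documents do not show this: the number of such patients cannot be derived and is probably very small among at most 19. Severity is minor. Confidence is high in the comparison of limits and lower in the intended unit.

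**What to change.** 1. In item 15 of 4.2.1, check the unit against the source document and correct mg/mL to mg/dL.
2. Add an ALT entry limit no looser than 5.3.2. Without liver metastases, ≤ 3 × ULN closes the gap; ≤ 2.5 × ULN would match the AST limit but excludes some patients whom 5.3.2 would allow to be dosed. With liver metastases, use ≤ 5 × ULN.
3. Make the Gilbert's limit the same in both sections. Preferably, add a Gilbert's provision (total bilirubin < 3.0 mg/dL) to the pre-ipilimumab check, which keeps the evident purpose of the entry allowance. Otherwise, lower the entry limit to ≤ 1.5 × ULN for Gilbert's patients without liver metastases. The choice is for the sponsor's clinicians.

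The cost is a wording amendment; the tests are already scheduled at screening and before dosing. A few patients with raised ALT, and under the second option in (3) a few with Gilbert's syndrome, would no longer qualify.

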### **1.3.6   *Ipilimumab in Malignant Melanoma***

#### **1.3.6.1            *Clinical Pharmacology Summary: ipilimumab monotherapy***

Ipilimumab has a terminal half-life of approximately 15.4 days. The expected in vivo degradation of monoclonal antibodies is to small peptides and amino acids via biochemical pathways that are independent of cytochrome P450 enzymes. The population PK of ipilimumab was studied with 785 subjects and demonstrated that PK of ipilimumab is linear and exposures are dose proportional across the tested dose range of 0.3 to 10 mg/kg, and the model parameters are time invariant. Upon repeated dosing of ipilimumab, administered every three weeks, minimal systemic accumulation was observed by an accumulation index of 1.5-fold or less and ipilimumab steady-state concentrations were achieved by the third dose. The ipilimumab clearance of 16.8 mL/h from population PK analysis is consistent with that determined by PK analysis. The terminal half-life (T-HALF) and Vss of ipilimumab calculated from the model were 15.4 days, and 7.47 L, which are consistent with that determined by non-compartmental analysis (NCA). Volume of central (Vc) and peripheral compartment were found to be 4.35 L and 3.28 L, respectively, suggesting that ipilimumab first distributes into plasma volume and subsequently into extracellular fluid space. Clearance of ipilimumab and Vc were found to increase with increase in body weight. Nevertheless, there was no significant increase in exposure with increase in body weight when dosed on a mg/kg basis, supporting dosing of ipilimumab based on a weight normalized regimen. Additional details are provided in investigator brochure.

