### ***Age and Sex***

Men and women of and over 18 years old.

Women of childbearing potential (WOCBP) must use appropriate method(s) of contraception. WOCBP should use an adequate method to avoid pregnancy for 23 weeks (30 days plus the time required for ipilimumab to undergo five half-lives) after the last dose of investigational drug

WOCBP include any female who has experienced menarche and who has not undergone successful surgical sterilization (hysterectomy, bilateral tubal ligation, or bilateral oophorectomy) or is not postmenopausal. Post menopause is defined as:

- 1) Amenorrhea  $\geq 12$  consecutive months without another cause or
- 2) For women with irregular menstrual periods and on hormone replacement therapy (HRT), a documented serum follicle stimulating hormone (FSH) level  $> 35$  mIU/mL.

Women who are using oral contraceptives, other hormonal contraceptives (vaginal products, skin patches, or implanted or injectable products), or mechanical products such as an intrauterine device or barrier methods (diaphragm, condoms, spermicides) to prevent pregnancy, or are practicing abstinence or where their partner is sterile (eg, vasectomy) should be considered to be of childbearing potential.

WOCBP must have a negative serum or urine pregnancy test (minimum sensitivity 25 IU/L or equivalent units of HCG) within 24 hours prior to the start of investigational product.

Men who are sexually active with WOCBP must use any contraceptive method with a failure rate of less than 1% per year. Men receiving ipilimumab and who are sexually active with WOCBP will be instructed to adhere to contraception for a period of 23 weeks after the last dose of investigational product. Women who are not of childbearing potential (i.e., who are postmenopausal or surgically sterile as well as azoospermic men do not require contraception).

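### Section 4.2.1 gives men two different contraception periods (2 months and 23 weeks), and Section 7.7.1 allows a 72-hour pre-dose pregnancy test where Sections 4.2.1 and 6.3.3 require 24 hours

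*Combined protocol and SAP*

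**What the plan says.** **Male contraception.** Section 4.2.1, Target Population, item 17: "Men should not father a child while receiving treatment with SGI-110 + ipilimumab, and for 2 months following completion of treatment". The next sentence adds: "Men with female partners of childbearing potential should use effective contraception during this time". Age and Sex, which follows in the same section, says: "Men receiving ipilimumab and who are sexually active with WOCBP will be instructed to adhere to contraception for a period of 23 weeks", counted from the last dose of investigational product. For WOCBP the same text also sets 23 weeks and explains it as "30 days plus the time required for ipilimumab to undergo five half-lives". No explanation is given for men. Section 1.3.6.1 supplies the half-life: "Ipilimumab has a terminal half-life of approximately 15.4 days".

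The two places also differ on method. Item 17 asks all men for two methods of birth control. Age and Sex asks men who are sexually active with WOCBP for any method with a failure rate below 1% per year.

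**Pre-dose pregnancy test.** Age and Sex requires a negative test "within 24 hours prior to the start of investigational product". Section 6.3.3 repeats the 24-hour limit and foresees that the screening test may have to be repeated for that reason. Section 7.7.1 sets 72 hours and refers to Section 6.1. The pregnancy-test row in Section 6.1 marks visits, including Week 0, and gives no interval in hours between test and dose.

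**How the criteria combine.** Section 4.2 states that "the following criteria MUST be met within 4 weeks prior to first dose", and item 1 of Target Population that "Subjects must fulfill all of the following inclusion criteria".

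**The concern.** Both pairs of rules are in current protocol text and address the same people at the same moments. Every man treated as planned receives ipilimumab, so a man who is sexually active with a WOCBP falls under both item 17 and Age and Sex. If he is told only what item 17 says, he stops contraception about 100 days before the date Age and Sex sets.

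A woman tested 48 hours before her first dose satisfies Section 7.7.1 but fails an inclusion criterion, and would need another test. Section 7.7.1 is the part of the safety chapter devoted to pregnancy-testing requirements, so staff may well look there first.

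What is at stake is protection of a pregnancy from exposure and clear instructions to participants. The protocol itself treats exposure through the father as relevant, because Section 7.7.2 asks for pregnancies in partners of male participants to be reported.

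**Working it through.** **Inputs**
- Male period, item 17: 2 months after treatment.
- Male period, Age and Sex: 23 weeks after the last dose.
- Ipilimumab terminal half-life, Section 1.3.6.1: 15.4 days.
- Five half-lives as used for the safety reporting period, Section 8.4.2: 70 days.
- Pregnancy-test window: 24 hours (Sections 4.2.1 and 6.3.3); 72 hours (Section 7.7.1).

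**1. The protocol's own figure of 23 weeks.** Formula: 30 days + 5 × half-life.
- With 15.4 days: 30 + 5 × 15.4 = 30 + 77 = 107 days; 107 / 7 = 15.3 weeks.
- With the 70 days of Section 8.4.2: 30 + 70 = 100 days; 100 / 7 = 14.3 weeks.
- As stated: 23 × 7 = 161 days.

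The figure is not reproduced. It exceeds its own explanation by 161 − 107 = 54 days, or by 161 − 100 = 61 days. To obtain 23 weeks the half-life would have to be (161 − 30) / 5 = 26.2 days.

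**2. Gap between the two male periods.** Two calendar months last 59 to 62 days, about 61 on average.
- Smallest gap: 161 − 62 = 99 days.
- Largest gap: 161 − 59 = 102 days.
- Typical gap: 161 − 61 = 100 days, about 14.3 weeks.

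**3. Two months against five half-lives.**
- With 77 days: short by 77 − 62 = 15 to 77 − 59 = 18 days.
- With 70 days: short by 70 − 62 = 8 to 70 − 59 = 11 days.

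The protocol offers the half-life basis for WOCBP only. This comparison therefore gives context and does not show what period men need.

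**4. Pregnancy-test window.** 72 − 24 = 48 hours wider in Section 7.7.1.

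**5. Does any other text settle it?** Section 6.1, to which Section 7.7.1 points, has no hour window for the test. The ±3 days in its treatment-phase header is a tolerance on visit dates, not an interval between test and dose. No rule in the protocol says that the stricter text prevails where sections differ.

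**The case against.** The strongest reply is that both texts can be obeyed at once. A man who uses contraception for 23 weeks also meets item 17, and a test within 24 hours also meets Section 7.7.1. The criteria are cumulative, Age and Sex comes directly after item 17, and it is worded as the instruction men will be given. With a single centre there is no between-site variation. This stands as far as it goes: the stricter rule is the sensible reading. But the reader has to infer it, and each weaker text looks complete on its own.

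Participants are informed through the consent documents, which were not available for this review. What men are actually told therefore cannot be verified. This limits the consequence that can be claimed, but the contradiction in the protocol remains.

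On the pregnancy test, the 72 hours may derive from the ±3-day visit window. That may explain the number without making it a test-to-dose rule. It can also be argued that Section 7.7.1 speaks of receiving product in general, so that 24 hours would then apply before every administration. However, its second paragraph deals separately with testing during the study, so the first paragraph is naturally read as the test before treatment starts.

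Finally, 23 weeks cannot be derived from the stated half-life, so it may seem odd to adopt it. That is a fair point for the sponsor. It does not remove the conflict, and 23 weeks is the longer period already in the protocol. The affected group is also small: at most 19 subjects are planned, and the duration point reaches only men sexually active with WOCBP.

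**Conclusion.** The concern holds on both counts, with high confidence. Item 17 ends male contraception 99 to 102 days before the date set in Age and Sex, and Section 7.7.1 allows a pregnancy-test window 48 hours wider than Sections 4.2.1 and 6.3.3. The size of the first gap depends only on the calendar length of two months and on counting both periods from the same last dose. The half-life comparison is not needed for the conclusion.

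This should be corrected because a weaker embryo-fetal safeguard stands in an eligibility criterion and in a safety section. It does not threaten the MTD evaluation or any efficacy analysis, and no effect on pregnancy risk has been estimated.

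**What to change.** 1. In item 17 of Section 4.2.1, replace the two-month period with 23 weeks after the last dose of investigational product.
2. In the first paragraph of Section 7.7.1, replace 72 hours with 24 hours. Adding that this means before the first dose would remove any doubt about later administrations.
3. As secondary wording, align the male method text in item 17 with Age and Sex. Whether a second method is required is the sponsor's choice.
4. The sponsor should also explain or correct the basis given for 23 weeks, since 30 days plus five half-lives of 15.4 days is 107 days. Whatever period is justified should then be used throughout.

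The cost is a wording amendment. Men who would have followed item 17 use contraception for about 100 more days. That includes any man who stops before his first ipilimumab dose, for whom Age and Sex sets no period. A WOCBP tested between 24 and 72 hours before dosing needs a repeat test, which Section 6.3.3 already foresees, and a Week 0 test is already scheduled.
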